#### Treatment period

Patients in the treatment group will be treated with Qingpeng ointment, and patients in the control group will be treated with placebo ointment. Patients in both groups will be given diclofenac sodium sustained-release tablets (DSSRT) as rescue medicine. Drugs for other underlying diseases such as antihypertensive drugs, hypoglycemic drugs, and hypolipidemic drugs are permitted to be taken during the treatment period. And other Chinese patent medicine are prohibited during the trial. When participants experience severe skin allergies at application site, or experience serious adverse events, investigators will advise them to discontinue using the study drug. The degree of joint pain, swelling, redness, and mobility will be scored and recorded on patient diary every day by patients, and the width and thickness of affected joints will also be measured and recorded every day by themselves. The course of treatment is seven days.

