#### Placebo group

In order to evaluate the absolute efficacy and safety of Qingpeng ointment for AGA and reduce the risk of bias, we chose placebo as comparison. Participants in control group will be treated with placebo ointment (produced by Tibet Cheezheng Tibetan Medicine Co., Ltd). The ingredients of placebo ointment include purified water, liquid paraffin, glycerinum, methylparaben, and food coloring. The placebo ointment is the same as Qingpeng ointment in texture, color, smell, and packaging. The usage of placebo ointment is the same as Qingpeng ointment.

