#### Rescue medicine

DSSRT (produced by Beijing Novartis Pharmaceutical Co., Ltd; specification: 75mg/tablet, 10 tablets/box) will be given to participants in both treatment group and control group as rescue medicine. Patients in both groups are recommended to take the rescue medicine only when the VAS score of joint pain is ≥ 7 points (scale of 0 to 10), which is scored by patients themselves. Patients will also be recommended not to take the rescue medicine when joint pain is reduced to a tolerable extent (VAS score reduce to less than 7 points). The recommended dose is one tablet per time, once daily, and the maximum dose is one tablet per time, twice a day.

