#### Allocation concealment and blinding

Sequentially numbered drug containers of identical appearance were used to achieve allocation concealment. Two hundred and six drug boxes with identical appearance were numbered as 001–206. According to the random sequence, Qingpeng ointment and placebo ointment were put into the corresponding numbered boxes, with three tubes of Qingpeng ointment or placebo ointment in each box. One box of DSSRT was also put into each drug box at the same time. Special personnel are assigned to manage the study drugs in each hospital, and the corresponding sequence of drugs will be distributed to each patient according to their recruitment sequence. Throughout the study, the investigators and the participants will not know which group the participants are assigned to. For each participant sequence, a corresponding emergency letter was made, which records the allocation result of that participant. When a participant experience serious adverse events and the allocation result needs to be known, investigators can open the emergency letter. The process of unblinding, including reasons, time, and treatment results, should be recorded on the case report form.

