#### Secondary outcomes

Secondary outcomes include changes in joint mobility degree and redness degree between baseline and treatment completion, changes in C-reactive protein and serum uric acid between baseline and treatment completion, and the remaining amount of rescue medicine at treatment completion.Joint mobility: Degree of joint mobility will be measured by participants, using a 0–4 points scale (0=the mobility is normal, and is not restricted; 1=the mobility is slightly restricted, but normal activities can still be performed; 2=the mobility is moderately restricted, patient is unable to perform general activities, but is able to take care of self daily life; 3=the mobility is severely restricted, pain is unbearable when the joint moves, patient is unable to take care of self daily life; 4=the joint is unable to move), at baseline, every day during treatment, and after 7-day treatment.Joint redness: Degree of joint redness will be measured by participants, using a 0-3 points scale (0=the skin color is normal; 1=the skin is slightly red; 2=the skin is obviously red; 3=the skin is dark red), at baseline, every day during treatment, and after 7-day treatment.C-reactive protein: Will be measured from a blood sample taken at baseline and after 7 days of treatment.Serum uric acid: Will be measured from a blood sample taken at baseline and after 7 days of treatment.Remaining amount of rescue medicine: Will be recorded after 7 days of treatment.

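### The rescue outcome counts tablets left from a 10-tablet box although 14 are permitted over 7 days, so it is capped and takes no account of time on treatment

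*Protocol article*

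**What the plan says.** All references are to the protocol article.

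- **Outcome.** Under Secondary outcomes: "Remaining amount of rescue medicine: Will be recorded after 7 days of treatment". The Discussion says that this quantity will serve as evidence of the ointment's efficacy. The abstract describes the outcome as the use of rescue medicine, which is a different quantity from what is left over.
- **Permitted use.** Under Rescue medicine, tablets are advised "only when the VAS score of joint pain is ≥ 7 points". "The recommended dose is one tablet per time, once daily", and "the maximum dose is one tablet per time, twice a day".
- **Supply.** The product is described as "specification: 75mg/tablet, 10 tablets/box". Under Allocation concealment and blinding: "One box of DSSRT was also put into each drug box at the same time". No further supply is mentioned.
- **Duration.** Under Treatment period: "The course of treatment is seven days".
- **Other records.** The Treatment visit section has combined medication over the treatment period recorded, in addition to the returned tablets. The diary items named under Treatment period are symptom scores and joint dimensions.
- **Dropout.** Sample size estimation allows for 20%. Statistical analysis applies last observation carried forward to dropouts. Data collection and management has investigators seek whatever outcome data they can from those who withdraw.

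**The concern.** Tablets left over measure rescue use properly only if two conditions hold: nobody runs out, and everybody is observed for the same time. The article's own figures do not secure either.

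If the box can be emptied within the permitted dosing, the heaviest users all share the value zero, and differences in need among them cannot be seen. If participants leave at different times, the number left reflects how long they stayed as well as how much they needed. A full box handed back on an early exit would then count as a good result. Since the quantity is meant to support efficacy, a difference between arms in heavy use or in early leaving could distort the comparison.

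Separately, the stated maximum and the stated supply do not agree with each other.

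**Working it through.** **Inputs, all from the article.** 10 tablets per box and at most 2 tablets a day, with 1 a day recommended (Rescue medicine); 1 box per kit (Allocation concealment and blinding); 7 days (Treatment period); 206 participants and 20% dropout (Sample size estimation). The article gives no figure for expected rescue use, so there is none to reproduce.

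**Step 1: supply against permitted maximum.**
- Supply: 1 × 10 = 10 tablets.
- Permitted maximum: 2 × 7 = 14 tablets.
- Shortfall: 14 − 10 = 4 tablets; supply covers 10/14 = 71%.
- Time to an empty box at the maximum: 10/2 = 5 days.

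**Step 2: who is affected by the cap.** Tablets left = max(0, 10 − tablets needed), so every need from 10 to 14 reads 0. A need of exactly 10 is still recorded correctly; information is lost from 11 upwards. If a days are at two tablets and the other days at no more than one, the largest need is 2a + (7 − a) = 7 + a.
- a = 3: at most 10, so not exceeded.
- a = 4: at most 11, so it can be exceeded.

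Exceeding the box thus requires at least 4 days at two tablets. This is necessary but not sufficient: 5 days at two and 2 days at none gives exactly 10. At one a day throughout, 10 − 7 = 3 remain and nothing is lost.

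**Step 3: effect of leaving early.** Tablets left at constant daily use:

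| Daily use | Leaves after day 2 | Completes 7 days |
|---|---|---|
| 1 tablet | 10 − 2 = 8 | 10 − 7 = 3 |
| 2 tablets | 10 − 4 = 6 | 0 (need 14, capped) |

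At the same daily use the early leaver has 5 or 6 more tablets left. A day-2 leaver at two a day (6 left) would even rank ahead of a completer at one a day (3 left). With 20% dropout this could concern 0.20 × 206 = 41.2, about 41 participants, if their raw counts were used.

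**Step 4: does scaling by time help?** Tablets taken per day on study, where taken = dispensed − returned:
- 1 a day: leaver 2/2 = 1.0; completer 7/7 = 1.0. The distortion is gone.
- 2 a day: leaver 4/2 = 2.0; completer 10/7 = 1.43, which is only a lower bound because the box is empty.

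Scaling removes the time effect but not the cap, so an empty box also has to be handled as censored.

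**The case against.** The strongest reply is that two a day is a daily ceiling and not a planned regimen. One a day is recommended, and only at a high pain score, with advice to stop below it. Sustained use at the ceiling on 4 or more days may be uncommon, and the article does not say how common. This stands, and it limits the cap to a minority of unknown size.

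Second, the outcome is tied to treatment completion. A day-2 leaver may simply have no value, and carrying an observation forward cannot supply one because the count is taken only once. This also stands: the early-leaver distortion is conditional. It is not removed, because investigators are to seek outcome data from those who withdraw and the article does not say how an early count would be entered.

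A reader might also infer three stronger things that the documents do not support:

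- **That rescue use is recorded nowhere else.** Combined medication is recorded at the treatment visit. Whether this includes dated rescue tablets is not stated, and a condensed article may omit diary fields.
- **That the data cannot show any link between rescue and pain.** Total use per participant, up to 10 tablets, can be compared between arms and related to the change in pain. What an undated count cannot do is tie a tablet to a particular day's score.
- **That rescue shrinks the pain difference by a known amount and so defeats the aim in** "In order to evaluate the absolute efficacy and safety of Qingpeng ointment for AGA". The article gives neither rescue rates by arm nor the effect of a tablet on the score, so any such figure would be invented. Analysing pain as recorded, with rescue open to both arms on the same terms, is a defensible choice.

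**Conclusion.** The point holds for the definition of one secondary efficacy outcome and for a conflict between two stated figures. Supply is 10 tablets against a permitted 14. The count is capped at zero left, with loss of information only for needs of 11 to 14, which take two tablets on at least 4 of 7 days. It is also unscaled: at one a day, 8 left for a day-2 leaver against 3 for a completer.

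This assumes that no re-supply takes place, since none is described. The early-leaver effect further assumes that returned counts are entered without regard to days on study. Neither the direction nor the size of any bias between the arms can be derived from the article. It does not show that the primary pain comparison is invalid.

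**What to change.** 1. Reconcile the maximum stated under Rescue medicine with the supply stated under Allocation concealment and blinding. Which of the two should change is for the trial team.
2. Before unblinding, redefine the outcome as tablets taken (dispensed minus returned) per day on study, together with any rescue use (yes/no). Treat an empty box as censored, meaning at least 10 tablets.
3. Where the diary or the combined-medication record holds dated rescue intake, use it to report rescue use by arm beside the pain result.

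Items 2 and 3 use data that the article already says are collected, plus the dates of leaving, so they work even if recruitment is complete. One limit remains: a per-day rate assumes fairly even use. If need falls as the flare settles, an early leaver's rate will be somewhat high, so days on study should be shown by arm.

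The cost is a reworded secondary outcome, a little more analysis and a protocol amendment, which under the Ethics section goes to the ethics committee of each of the three centres and to the registry.

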#### Safety outcomes

Vital signs and general physical examination: Will be tested and recorded at baseline visit, treatment visit, and follow-up visit.Adverse events: Adverse events during the trial will be recorded in detail.

### Sample size estimation

This study includes two primary outcomes: joint pain and joint swelling. Sample size was estimated based on these two primary outcome measures. Estimation according to joint pain was based on results from a previous study [23]. In this study, 47% participants in treatment group (Qingpeng ointment plus diclofenac sodium tablets) had significant relief of joint pain (the score of joint pain degree measured by a self-developed scale reduced by 6 points), and 25% participants in control group (diclofenac sodium tablets) had significant relief of joint pain. On the basis of a 5% type I error rate (*α*=0.05) and a power of 90% (*β*=0.1), the sample size of each group was 82. Assuming a 20% dropout rate, a total of 206 participants should be recruited, with 103 participants in each group.

Estimation according to joint swelling was likewise based on results from another previous study [19], which established score of joint swelling measured by a 0–3 points scale as 0.45 points after receiving Qingpeng ointment plus etoricoxib tablets, and the estimated standard deviation is 0.37. Score of joint swelling after receiving vaseline plus etoricoxib tablets is 0.87, and the estimated standard deviation is 0.64. On the basis of a 5% type I error rate (*α*=0.05) and a power of 90% (*β*=0.1), the sample size of each group was 27. Assuming a 20% dropout rate, a total of 68 participants should be recruited, with 34 participants in each group.

Based on these results, we chose the larger sample size of 206 participants, with 103 participants in each group.

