### Statistical analysis

Statistical analysis will be performed using SAS 9.2 software, with a statistical significance of *p* value less than 0.05. Normally distributed continuous variables will be described using mean ± standard deviation (SD), and non-normally distributed continuous variables will be described using median and interquartile range (IQR). Categorical variables will be described using frequencies and percentages. Primary outcomes will be analyzed according to the intention-to-treat principle. Intra-group differences of continuous variables will be tested for significance using paired-samples *t* test when the data is normally distributed, and will be tested using non-parametric test when the data is non-normally distributed. Between-group differences of continuous variables will be tested for significance using independent-samples *t* test when the data of the two groups are normally distributed and have equal variance, and will be tested using non-parametric test when the data of the two groups are non-normally distributed or have unequal variances. Chi-square test will be used for categorical data. Data from participants who drop out from this study will be implemented by the last-observation-carried-forward (LOCF) method. Interim analyses will not be performed. For the co-primary endpoints, Bonferroni correction will be performed to correct multiplicity.

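### The 82 per group for pain that fixes the trial at 206 matches 90% power only with a one-sided 5% test; sidedness is unstated, and two-sided power at the planned Bonferroni level is about 76% to 86%

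*Protocol article*

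**What the plan says.** In the protocol article, Sample size estimation, the pain calculation starts from an earlier study in which "47% participants in treatment group (Qingpeng ointment plus diclofenac sodium tablets) had significant relief of joint pain" and "25% participants in control group (diclofenac sodium tablets) had significant relief of joint pain". At α = 0.05 and 90% power it concludes that "the sample size of each group was 82". Allowing 20% dropout gives 103 per group.

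The swelling calculation uses means of 0.45 (SD 0.37) and 0.87 (SD 0.64) with the same error rates and concludes that "the sample size of each group was 27", or 34 after dropout. The larger result, 206 in total, is adopted.

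Statistical analysis plans t tests or non-parametric tests for continuous data, "Chi-square test will be used for categorical data", and judges results "with a statistical significance of *p* value less than 0.05". No direction is given. The same section promises a Bonferroni correction for the co-primary endpoints, intention-to-treat analysis of the primary outcomes, and LOCF for dropouts. Neither one-sided nor two-sided appears anywhere in the article.

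**The concern.** The inputs, the error rates and the result are all printed, so the calculation can be checked, and under the usual two-sided convention it does not close. Pain is the calculation that determines how many patients are recruited. If its 90% rests on an undeclared one-sided 5% test, the trial has less power for pain than the article says, and a null pain result would be read against assurance that the design does not provide. The planned Bonferroni correction widens the gap, because the sizing used the full 0.05.

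**Working it through.** **Inputs** (Sample size estimation): p1 = 0.47, p2 = 0.25, so d = 0.22 and the mean proportion is 0.36; swelling difference 0.87 − 0.45 = 0.42, SDs 0.37 and 0.64; power 90% (z = 1.2816); dropout 20%; 1:1 allocation. Critical values: 1.6449 (one-sided 0.05), 1.9600 (two-sided 0.05), 2.2414 (two-sided 0.025).

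**Step 1: reproduce the printed figures.**

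Pain, pooled variance in both terms: n = (zα + zβ)² × 2 × 0.36 × 0.64 / 0.22² = (zα + zβ)² × 9.521.
- One-sided 0.05: 8.564 × 9.521 = 81.5, rounded up to **82**, as printed.
- Two-sided 0.05: 10.507 × 9.521 = 100.04, rounded up to 101.

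Swelling: n = (zα + zβ)² × (0.37² + 0.64²) / 0.42² = (zα + zβ)² × 3.098.
- One-sided 0.05: 26.5, rounded up to **27**, as printed.
- Two-sided 0.05: 32.6, rounded up to 33.

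Dropout: 82/0.8 = 102.5, so 103; 27/0.8 = 33.75, so 34. Both are as printed.

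**Step 2: could another two-sided formula give 82?** At 90% power and two-sided 0.05, pain needs 95 (unpooled), 98 (pooled under the null, unpooled under the alternative), 98 (arcsine), 101 (pooled in both terms) or 107 (continuity-corrected). None is near 82. Swelling needs 31 to 34 depending on the variant, not 27. Two separate calculations, one binary and one continuous, both land exactly on the one-sided value.

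**Step 3: power for pain at the sizes the trial may analyse.** Using pooled variance under the null and unpooled under the alternative: zβ = [0.22√n − zα√0.4608] / √0.4366, where 0.4608 = 2 × 0.36 × 0.64 and 0.4366 = 0.47 × 0.53 + 0.25 × 0.75. For n = 82 at two-sided 0.05: (1.992 − 1.330) / 0.661 = 1.001, a power of 84.2%.

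| Level | 82 analysed | 103 analysed | n per group for 90% |
|---|---|---|---|
| One-sided 0.05 | 90.7% | 95.4% | 80–82 |
| Two-sided 0.05 | 84.2% | 91.4% | 98–101 |
| Two-sided 0.025 (Bonferroni, two outcomes) | 76.2% | 85.9% | 116–119 |

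In the last column, the lower value comes from the step 3 formula and the upper from the formula that yields 82. With 20% dropout, 98 to 101 becomes 123 to 127 randomised per group (246 to 254 in total), and 116 to 119 becomes 145 to 149.

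**Step 4: swelling at the real trial size.** With 82 per group, two-sided power is 99.9% at 0.05 and 99.8% at 0.025.

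**The case against.** - **Sidedness is not written.** A reader might infer that the article plans two-sided tests and so contradicts itself. It does not say so; two-sided is the ordinary reading of an undirected 0.05 threshold. The chi-square sentence adds little, because the primary outcomes are changes in continuous measures, which go to t or non-parametric tests. This stands: the accurate charge is that sidedness is undeclared and the printed number fits only a one-sided test. A one-sided intention would not rescue the claim either. Bonferroni over two outcomes would put each test at one-sided 0.025, which has the same critical value as two-sided 0.05 and gives 84% at 82.

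- **Swelling is not underpowered.** It is tempting to say that the stated power fails for both outcomes, since 27 per group gives only about 83% to 84% two-sided. Nobody will run that trial. At 82 per group swelling exceeds 99%, so 27 serves only as a second sign of the one-sided value.

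- **Dropouts may stay in the analysis.** A reader might infer a type II error of 16% outright. That holds only with 82 analysed. The plan is intention-to-treat with LOCF, and investigators will pursue outcome data after withdrawal. If all 103 count and carried-forward values do not dilute the effect, unadjusted two-sided power is nominally 91%, and the 90% target is met from 98 analysed. This stands before Bonferroni but not after it: at 0.025, even 103 gives 86%.

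- **The formula matters.** The 98 and the 82 come from different formulas; the formula that yields 82 gives 101 two-sided. Hence a range is reported.

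**Conclusion.** The point holds for pain, the outcome that fixes the trial size. The stated 90% corresponds to an undeclared one-sided 5% test. Read two-sided, power for pain is 84% with the 82 per group that the plan expects after dropout, and at best 91% with all 103. At the planned Bonferroni level it is 76% and 86%, so 90% is not reached either way.

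These figures assume that:
- the tests are two-sided;
- Bonferroni is applied over the two primary outcomes named in the sample size section. If pain VAS, swelling VAS, width and thickness were counted as four tests (two-sided 0.0125), pain power would be 67% at 82 and 79% at 103;
- LOCF does not dilute the effect;
- the responder rates of 47% and 25% apply.

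The last assumption also limits what the figures mean. They describe a responder proportion on another study's self-developed scale. The primary pain outcome here is a change in VAS, and the article gives no inputs from which its power could be computed. The documents therefore do not support reading 76% or 86% as the power of the primary pain analysis; they show only that the printed justification does not deliver its stated 90%.

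**What to change.** Revise the sample size section and add one sentence to the statistical analysis section:

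1. State that the tests are two-sided. If one-sided 5% tests were intended, declare and justify that instead.
2. Correct the evaluable numbers per group needed for 90% power: about 98 to 101 for pain and 33 for swelling at two-sided 0.05; about 116 to 119 for pain at two-sided 0.025. Name the formula used.
3. Replace the 90% claim for pain with the power that 206 gives at the Bonferroni-adjusted two-sided level: 76% with 82 analysed and 86% with 103. The unadjusted 84% and 91% may be given beside them but not alone, since the plan will not test at that level.
4. Say that these figures refer to the responder proportion used for sizing and not to the change in pain VAS.

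The cost is some rewording. No extra patients are needed, and no endpoint or test changes. The price is a less favourable power statement.
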